### Data collection and management

Screening, baseline, 3-month, and 6-month interviews will be conducted by research assistants, each provided with same training, and blinded to group allocation. Reminders will be given to participants 2–3 days prior to each interview. Four attempts, using different methods of contact, will be made for participants we have been unable to reach for 3-month or 6-month follow-up interviews. For individuals who withdraw from the study, the reasons for withdrawal will be documented, if discoverable.

At screening, each individual will be assigned a Study ID that will be used for all subsequent data collection and analysis in order to maintain anonymity. A list linking Study ID to personal identifying information (name, age, contact information) will be stored in a password-protected file to which only two of the study investigators and the research assistants will have access to. Hard copies of interview data will be kept in a locked filing cabinet at the main site (Queen’s University). As data are collected during the study, the research assistants will code and enter the data into a database created in IBM SPSS Statistics Version 24. All data files will be stored on an encrypted drive on the Queen’s University server to which only two of the study investigators and research assistants will have access. Data back-ups will occur daily using an encrypted external hard drive.

### Website usage data

User analytic data will be collected from the website (from both groups) in order to track the number of times the site is accessed, length of each visit, specific pages visited, time spent on each page, which worksheets and links were accessed and how often, and to capture all fatigue ratings and goal data entered. These data will be collected to identify delivery fidelity (did participants access all components of the website) and for descriptive analysis of usage patterns and impact of use on outcomes.

### Statistical analysis

All data will be analyzed in IBM SPSS Statistics Version 24. Scores on all outcome measures will be calculated according to manual instructions for each measure. Unusually high or low values will be checked against the raw data to confirm accuracy. Descriptive statistics will be calculated for each variable for both the intervention and usual care control group. Score distributions will be checked to ensure that distributional assumptions are met for the hypothesis testing step of the analysis.

The MS INFoRm and usual care groups will be compared on baseline measures and key demographic and disease-related variables that may influence study outcomes (e.g. age, disease duration, education level) to test equivalence of groups. Independent samples t-tests will be used for continuous variables with a normal distribution, Mann Whitney U tests for non-normally distributed data, and chi-square tests for categorical variables. If differences are found, these variables will be used as covariates during hypothesis testing to ensure that group differences at baseline are not responsible for differences in outcomes.

For individuals lost to follow-up, their data will be used in the statistical analysis in the effectiveness analysis as per an intention to treat approach [40]. These individuals will remain in the same group as randomized. The advantage of this approach is that the estimated effect of the intervention will reflect the effect that would actually be achieved in the real world (i.e., effectiveness analysis) when people have differential motivation to use MS INFoRm. Missing data will be imputed using the strategy of last observation carried forward, as this is the most conservative [41].

Hypothesis 1 states that the MS INFoRm group will show significant reductions in fatigue impact compared to the usual care control group. In order to test hypothesis 1, changes between baseline and 3-month scores on the MFIS will be compared between the MS INFoRm group and the usual care control group using an independent t-test. If the testing for group equivalence indicates that there are baseline differences between the groups at baseline, an analysis of variance with covariates will be used to test hypothesis 1. A *p* < 0.05 will be used as the significance value. In order to test efficacy, or whether MS INFoRm works when delivered as intended, data from only those individuals who have complete baseline and 3-month data and have accessed all of the website content at least once will be used in the analysis. In order to test effectiveness, participants who have missing 3-month scores will be assigned a change score of zero.

Hypothesis 2 states that the MS INFoRm group will show significant improvements in self-efficacy for managing MS fatigue, self-reported cognitive function, participation and autonomy, and significant reductions in depression, compared to the usual care control group. The analysis will use the same approach as hypothesis 1, using zero-value change scores for individuals lost to follow-up. A Bonferroni adjustment will be applied for multiple testing, and therefore the significance value will be set at *p* < 0.0125 (0.05/4 tests).

Hypothesis 3 states that the beneficial effects of MS INFoRm will be maintained at 6-month follow-up. To address this hypothesis, a mixed-effect ANOVA will be used with an unstructured variance-covariance structure, a random intercept and terms for both a linear and quadratic trend. A quadratic trend would be characterized by a sharp improvement immediately post-intervention (3-months), followed by a gradual stabilization of improvement. The five measures (MFIS, MSSES, PDQ, CES-D, and IPA) will be modelled simultaneously and individually. When modelled simultaneously, a significance value of *p* < 0.05 will be used. When modelled individually, a Bonferroni adjustment will be applied for multiple testing, and therefore the significance value will be set at *p* < 0.01 (0.05/5 tests).

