### Group allocation

Group allocation will be based on a random permutated block design, using computerized random number generation. This design was selected because it ensures a 1:1 allocation ratio between the intervention group and the control group and because it will effectively reduce any risk of a systematic bias that may confound the treatment effect (i.e., people from the same MS clinic enrolling sequentially). The block size, which is fixed, will not be disclosed, to ensure concealment. One hundred people will be allocated to the MS INFoRm group and 100 to the usual care control group.

All eligible participants will be provided with a study identification number and password to access the MS INFoRm website. Using the block randomization process described above, each study ID has been assigned to one of the two groups by two of the study investigators. A password-protected file, and the MS INFoRm administrator website, which includes the group allocation for each Study ID, is only be accessible by two of the study investigators. Upon login, participants in the MS INFoRm intervention group will be directed to the intervention website whereas participants in the usual care control group will be directed to the usual care website. Participants will be provided with access to the website for 3-months from time of baseline assessment. Participants will access the website at their own volition, and not be directed on how often to use it as the nature of the intervention is self-directed, in order to replicate real-world use.

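### The primary and secondary tests use change-score t-tests, with covariates added only after positive baseline significance tests: valid on average, but inefficient and dependent on chance imbalance

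*Protocol article*

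**What the plan says.** All of this is in the Statistical analysis section of the protocol article. For hypothesis 1, MFIS changes from baseline to 3 months "will be compared between the MS INFoRm group and the usual care control group using an independent t-test". Before that, the arms are compared on the baseline measures and on "key demographic and disease-related variables that may influence study outcomes (e.g. age, disease duration, education level", by t-test, Mann-Whitney test or chi-square test. The stated purpose is "to test equivalence of groups". The consequence is also stated: "If differences are found, these variables will be used as covariates during hypothesis testing". In that case "an analysis of variance with covariates will be used to test hypothesis 1" in place of the t-test.

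Hypothesis 2 (self-efficacy, perceived cognition, depression, participation and autonomy) is analysed in the same way. For hypotheses 1 and 2 no covariate is included unconditionally, although Table 2 schedules the baseline value of every outcome for all participants. No significance level is given for the baseline tests. A missing 3-month score counts as zero change in the effectiveness analysis.

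**The concern.** Three things are wrong with the rule as stated.

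- **The inference.** The baseline comparisons are tests of difference. A non-significant result does not show that the groups are equivalent. In a randomised trial a baseline difference arises by chance, so the test says nothing about whether adjustment is worthwhile.
- **The model.** Which variables enter the primary analysis, and whether any do, is settled by chance imbalance among the candidates. The primary model is therefore not fixed until the baseline data are in.
- **The precision.** A change score fixes the coefficient of baseline at 1. ANCOVA estimates it. When the correlation between the two scores is below 1, the change score carries more variance than it needs to. It also over-corrects a chance baseline imbalance, because of regression to the mean.

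At stake is power on the primary and all four secondary outcomes in a trial that itself expects difficulty in recruiting.

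**Working it through.** **Inputs from the article.** Allocation: "One hundred people will be allocated to the MS INFoRm group and 100 to the usual care control group". Primary level: "A *p* < 0.05 will be used as the significance value" (taken as two-sided; the article does not say). Attrition of up to 34% (Sample size). Zero change for missing 3-month scores (Statistical analysis).

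**Assumptions.** Correlation r of 0.5 to 0.8 between baseline and 3-month scores; equal SD s at both times; missingness m equal in the arms and unrelated to the scores; baseline tests at 0.05.

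**The plan's own figure.** The total of 200 comes from a mixed model with pilot estimates. The article does not print the effect, SD, correlation or power, so 200 cannot be reproduced here; that is not part of this point. For orientation, 100 per arm gives a change-score t-test 80% power at (1.960 + 0.842) × √(2/100) = 0.396 SDs of change.

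**1. Precision.** Per participant, the change-score variance is 2s²(1 − r) and the ANCOVA residual variance is s²(1 − r²). The ratio is (1 + r)/2. Setting a fraction m of changes to zero makes the 3-month score equal baseline for those people, so the effective correlation becomes r(1 − m) + m and the ratio becomes 1 − (1 − m)(1 − r)/2. At r = 0.5 and m = 0.34 this is 1 − 0.66 × 0.25 = 0.835. Dividing 200 by the ratio gives the number of participants a change-score analysis would need for the same precision.

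| r | Ratio, complete data | 200 worth | Ratio, 34% zeros | 200 worth |
|---|---|---|---|---|
| 0.5 | 0.75 | 267 | 0.835 | 240 |
| 0.6 | 0.80 | 250 | 0.868 | 230 |
| 0.7 | 0.85 | 235 | 0.901 | 222 |
| 0.8 | 0.90 | 222 | 0.934 | 214 |

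**2. Power.** The effect is set where the t-test has 80% power with complete data. By formula, ANCOVA then has 89.9%, 87.9%, 86.0% and 84.0% for r = 0.5, 0.6, 0.7 and 0.8. A simulation (20,000 runs per scenario, 100 per arm) added a simplified form of the rule: test baseline MFIS at 0.05, use ANCOVA if positive, otherwise the change-score t-test. Power in %, as t-test / rule / ANCOVA:

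| r | Complete data | 34% zeros |
|---|---|---|
| 0.5 | 79.5 / 80.6 / 89.7 | 61.2 / 61.6 / 68.4 |
| 0.6 | 79.5 / 80.3 / 87.2 | 61.3 / 61.6 / 67.0 |
| 0.7 | 79.7 / 80.4 / 85.3 | 61.0 / 61.3 / 65.3 |
| 0.8 | 79.6 / 80.1 / 83.2 | 61.3 / 61.4 / 63.9 |

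The rule recovers almost none of the loss, because under randomisation the baseline MFIS test is positive only about 5% of the time. The general fall to about 61% comes from the zeros diluting the effect, not from the choice between t-test and ANCOVA.

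**3. Type I error.** Under the null, the simulated rule rejected 4.2% to 4.7% of the time with complete data and 4.6% to 4.8% with 34% zeros. Among runs with a baseline imbalance just short of significance (z from 1.5 to 1.96), the unadjusted t-test rejected about 7% to 10% of the time, or about 6% to 9% with zeros.

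**4. Residual imbalance.** A chance baseline difference D leaves an expected difference in change of (1 − r)D in the opposite direction: the arm that starts worse appears to improve more. The largest D that passes as non-significant is 1.96 × √(2/100) = 0.28 SD. The residual is 0.5 × 0.28 = 0.14 SD at r = 0.5 and 0.3 × 0.28 = 0.08 SD at r = 0.7.

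**5. Chance that the model switches.** With k independent baseline tests at 0.05, the chance of at least one positive is 1 − 0.95^k: 14% for k = 3, 26% for k = 6, 40% for k = 10. The article does not fix k. Correlated variables, which are plausible among these scales, lower these figures.

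**The case against.** The rule is written down in advance, and its trigger is baseline data, not outcomes. The demographic and disease variables are limited to those thought to influence outcome, so the pool has some prognostic basis before imbalance decides among them. The full list and the level of the baseline tests may be in a fuller document. The change-score t-test is unbiased over randomisation. All of this stands, and it limits the point to efficiency and an unfixed model.

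Four stronger readings are tempting, and the documents do not support them.

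- *The rule inflates the false-positive rate.* The simulated overall rate was at or below nominal. The excess appears only conditionally, near the threshold of the baseline test.
- *Baseline MFIS is left out, so an imbalance of 0.28 SD goes unadjusted.* The change score already subtracts baseline. What remains is (1 − r) times the imbalance, with the sign reversed.
- *ANCOVA would make 200 participants worth 235 to 267.* Those figures need complete data and r of 0.5 to 0.7. Under the protocol's zero-change rule at 34% attrition, the same r gives about 222 to 240. The article hopes to keep attrition below the pilot's rate, so the truth may lie between.
- *Covariates are chosen without regard to prognosis.* The text filters the demographic and disease candidates on presumed influence first.

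None of this defends the conditional rule. Under it, a strong candidate predictor that is already collected enters as a covariate only by accident.

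**Conclusion.** The point holds as a matter of efficiency and of an unfixed primary model, and it should be corrected. The primary test is not invalid. Always adjusting for the baseline score would reduce the variance to 0.75 to 0.90 of the change-score variance with complete data, or about 0.84 to 0.93 with 34% of changes set to zero. That is about 4 to 10 or about 3 to 7 points of power respectively. These sizes rest on an assumed r of 0.5 to 0.8, equal SDs, and missingness that is equal between arms and unrelated to the scores. The gain shrinks towards zero as r approaches 1. The chance of a switch of model rests on an assumed number of independent tests at 0.05. The direction of the conclusion needs none of these exact values, only an r below 1. The fault lies in a rule that the article states, so it is not a detail left to an analysis plan.

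**What to change.** For the primary outcome and each secondary outcome, prespecify one ANCOVA of the 3-month score (or the change) on group that always includes that outcome's own baseline score. Fix any further prognostic covariates in advance and include them whatever imbalance is observed. Delete the baseline significance tests and the conditional covariate rule, and present baseline characteristics descriptively by arm. Add one sentence on how missing 3-month scores enter the ANCOVA.

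The cost is a wording amendment. Recruitment began in January 2018, and the article sends protocol changes to all the ethics boards, of which it names three. No new data or extra participants are needed, since the baseline scores are already scheduled. The change is best made before outcomes are examined by group.

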**Methods/Design:**

Parallel group, two arm, double-blinded superiority trial with a 1:1 allocation. Two hundred persons with MS will be randomly assigned to either an intervention (MS INFoRm) or usual care control group in which they will be given 3-month access to either the MS INFoRm website (intervention group) or a control webpage containing widely available resources on MS fatigue (control group). Baseline, immediate post-intervention (3-months), and follow-up (6-months post intervention) evaluations will take place on primary (Modified Fatigue Impact Scale) and secondary (Multiple Sclerosis Self-Efficacy Scale, Perceived Deficits Questionnaire, Center for Epidemiologic Studies Depression Scale, and Impact on Participation and Autonomy Questionnaire) measures. Hypothesis testing will involve independent samples t-tests and mixed effects ANOVAs.

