Our first aim is to determine the effectiveness and efficacy of 3-month use of MS INFoRm on fatigue impact among persons with MS. Our primary outcome will be measured using the Modified Fatigue Impact Scale (MFIS) [23]. We hypothesize that the MS INFoRm group will show significant reductions in fatigue impact compared to the usual care control group.

### Specific aim 2

Our second aim is to determine whether 3-month use of MS INFoRm results in improvement in secondary outcomes of self- efficacy for managing MS fatigue, self-reported cognitive function, depression, and participation and autonomy. The measures we will use to evaluate these outcomes are the Multiple Sclerosis Self-Efficacy Scale (MSSES) [24], the Perceived Deficits Questionnaire (PDQ) [25], Center for Epidemiologic Studies Depression Scale (CES-D) [26], and Impact on Participation and Autonomy Questionnaire (IPA) [27] respectively. We hypothesize that the MS INFoRm group will show significant improvements in self-efficacy for managing MS fatigue, self-reported cognitive function, participation and autonomy, and significant reductions in depression, compared to the usual care control group.

### Specific aim 3

Our third and final aim is to determine whether any improvements in primary and secondary outcomes are maintained among the MS INFoRm users after 6-months. We hypothesize that the beneficial effects of MS INFoRm will be maintained at 6-month follow-up.

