### Sample size

We seek to recruit a total of 200 individuals. The total number of individuals to be recruited is based on calculations of sample size and power for a balanced independent-groups mixed effect model with three time points for our primary outcome (i.e., fatigue impact at baseline, 3 months, 6-months post use). The effect sizes, variances and covariance estimates were obtained from our pilot results [21]. Calculations take into account potential attrition over time, which could be as high as 34% based on our pilot study. This high attrition rate, however, was likely due to limited persistence of research staff for follow-up assessments, which we will attempt to remediate in the proposed project.

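### Carrying the last observation forward biases Hypothesis 3 toward a maintained benefit if the benefit wanes, so it is not conservative for that aim

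*Protocol article*

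**What the plan says.** The Statistical analysis section describes an intention-to-treat effectiveness analysis that keeps participants lost to follow-up in their randomised group. It closes that paragraph with: "Missing data will be imputed using the strategy of last observation carried forward, as this is the most conservative".

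The same section then takes the hypotheses in turn. For the effectiveness test of Hypothesis 1, "participants who have missing 3-month scores will be assigned a change score of zero". Hypothesis 2 follows the same approach. At month 3 the only earlier score is baseline, so zero change and carry-forward are the same thing there.

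For the third aim, "Hypothesis 3 states that the beneficial effects of MS INFoRm will be maintained at 6-month follow-up". The model is "a mixed-effect ANOVA will be used with an unstructured variance-covariance structure, a random intercept and terms for both a linear and quadratic trend", and the pattern looked for is stated: "A quadratic trend would be characterized by a sharp improvement immediately post-intervention (3-months), followed by a gradual stabilization of improvement". No missing-data rule is given for this hypothesis. The significance level is 0.01 for each of the five measures modelled individually and 0.05 when they are modelled together.

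The last visit is six months after the three-month use period, month 9 in Table 2. On dropout, the Sample size section says: "Calculations take into account potential attrition over time, which could be as high as 34" per cent, a figure taken from the pilot.

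**The concern.** Whether a single-value imputation is conservative depends on the question. At month 3, carrying baseline forward assigns no benefit to those lost, which works against the intervention. At month 9 the question is whether a gain already made persists. Carrying the month-3 score forward assigns full persistence to everyone lost after month 3, which is the plateau that the quadratic term is meant to show. If benefit in fact wanes, and that is the alternative this aim has to be able to detect, the imputation hides part of the loss. It also enters exact zeros for the month 3-to-9 change as if they had been observed, so the uncertainty of that change is understated.

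At stake is the interpretation of a positive answer to Aim 3: part of the apparent persistence could come from the imputation rule.

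**Working it through.** **Inputs from the article.** 100 per arm (Group allocation); attrition up to 34% (Sample size); individual-model level 0.05/5 = 0.01, which reproduces. Effect sizes, variances and covariances are not printed, so the following are assumptions: 0.5 SD effect at month 3, none at month 9, change-score SD 1, correlation 0.6 between the two change scores, dropout unrelated to outcome and equal in both arms, nobody returning after a missed visit. A t-test on change from baseline to month 9 stands in for the mixed model.

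**Step 1, bias.** Let E be the true month-3 effect, r the share truly retained at month 9, m3 the share missing from month 3 on, and m9 the share missing at month 9. Under carry-forward:

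- effect at month 3 = (1 − m3)E
- effect at month 9 = (m9 − m3)E + (1 − m9)rE

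With all dropout after month 3 (m3 = 0), the apparent share retained is m9 + (1 − m9)r:

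| Missing only at month 9 | True share 0 | True share 0.5 | True share 1 |
|---|---|---|---|
| 10% | 0.10 | 0.55 | 1 |
| 20% | 0.20 | 0.60 | 1 |
| 34% | 0.34 | 0.67 | 1 |

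These shares depend on neither E nor the correlation.

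**Step 2, false-benefit rate when r = 0.** Write b = m9 − m3. The spurious effect is 0.5b. The variance of the month-9 change is (1 − m3) + 0.25b(1 − b) in the intervention arm and 1 − m3 in the control arm. The critical values of t on 198 degrees of freedom are 1.972 (0.05) and 2.601 (0.01).

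- 20%, all after month 3: effect 0.10; SE = √((1.040 + 1)/100) = 0.143; ratio 0.70. P(Z > 1.972 − 0.70) = 10.2%; P(Z > 2.601 − 0.70) = 2.9%.
- 34%, all after month 3: effect 0.17; SE = √((1.056 + 1)/100) = 0.143; ratio 1.19. Rates 21.6% and 7.9%.
- 34%, half before month 3 (b = 0.17): effect 0.085; SE = √((0.865 + 0.83)/100) = 0.130; ratio 0.65. Rates 9.4% and 2.6%.
- 34%, all before month 3 (b = 0): effect 0; rates nominal.

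The nominal rates in the favourable direction are 2.5% and 0.5%. Simulation under the same assumptions agrees: 10.4% and 3.4%; 20.9% and 7.6%; 9.8% and 2.6%. If 0.6 is instead the correlation between raw scores, with 0.5 in raw-score SDs, the first two cases become 12.3% and 3.3%, and 26.6% and 10.1%. With observed scores only, the estimated month-9 effect in that simulation is about zero and the rates are close to nominal.

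**Step 3, the within-arm course.** With r = 0 and 34% missing at month 9, the apparent loss in the intervention arm is 0.66 × 0.50 = 0.33 SD instead of 0.50 SD, whenever dropout occurs. If it all occurs before month 3, the month-3 effect shrinks to 0.33 SD as well, so no false share is retained.

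**Step 4, a direct test of waning.** For the between-arm month 3-to-9 contrast, the variance of the change is 2(1 − 0.6) = 0.8. At 34% missing only at month 9:

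- Observed scores: SE = √(2 × 0.8/66) = 0.156; ratio 0.50/0.156 = 3.21.
- Carry-forward: arm variances 0.66 × 0.8 + 0.66 × 0.34 × 0.25 = 0.584 and 0.66 × 0.8 = 0.528; SE = √(1.112/100) = 0.105; ratio 0.33/0.105 = 3.13.

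The estimate and its standard error shrink together, so simulated power at 0.05 barely moves: 87.8% with carry-forward, 88.6% with observed scores.

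**The case against.** **Scope.** The carry-forward sentence sits in a paragraph on the effectiveness analysis, and the Hypothesis 3 text names a model that can use incomplete records. One could read Hypothesis 3 as unimputed. That reading is possible, but the sentence carries no exception and no other rule is given for this hypothesis, so carry-forward is the natural reading. If the other was meant, the text should say so.

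**Stronger readings.** A reader might infer that the rule settles Hypothesis 3 in advance. It does not. It acts only through participants seen at month 3 and missing at month 9, and people lost earlier carry baseline forward. Even at 34% with complete waning, two thirds of the loss stays visible. If benefit holds fully there is no bias, and if it grew after month 3 the rule would understate it.

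A reader might also take 21% as the error rate of the plan. That figure puts all 34% after month 3, assumes complete loss of benefit, and uses 0.05 for a single-outcome test where the plan sets 0.01. The article treats 34% as an upper value, attributes it to limited staff persistence in the pilot, and plans reminders and four contact attempts. It gives no split of attrition by visit.

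**Choice of test.** The error rate belongs to a between-arm comparison at month 9. A direct test of waning keeps nearly the same power, as Step 4 shows. This stands: the harm lies in the estimate of what is retained and in any claim of continuing benefit at month 9, not in a general loss of ability to detect waning.

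**Conclusion.** The point holds in bounded form. As written, carry-forward extends to Hypothesis 3, and calling it most conservative is wrong for that aim. If benefit wanes, the month-9 effect is overstated by the share missing only at month 9 multiplied by the effect lost. That needs only dropout unrelated to outcome and equal across arms.

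The error rates also rest on the assumed 0.5 SD effect, complete loss by month 9 and the stand-in t-test. At the planned 0.01 they run from nominal (0.5%, all dropout before month 3) through 2.6% (34%, half before month 3) to about 8% (34%, all after). At 0.05 the corresponding range is 2.5% to about 21%.

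Severity is should-fix. The primary comparison uses month-3 change and is not touched by this mechanism.

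**What to change.** Four changes to the analysis text for Hypothesis 3:

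1. State that last observation carried forward is not used for this hypothesis.
2. Fit the mixed model already planned to the observed scores, including participants with incomplete records. This is valid if data are missing at random.
3. Drop the claim that carry-forward is the most conservative choice for this aim.
4. Add a sensitivity analysis that departs from missing at random, for example one in which intervention participants missing at month 9 return toward baseline or the control mean. Random dropout is itself an assumption, and those who lose benefit may be the ones who leave.

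Reporting the numbers missing at month 3 and only at month 9, by arm, would let readers judge how much this matters. The cost is a few sentences and one extra model run, with no new data collection and no change to the sample size.

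### Hypothesis 1 has two analyses under one unadjusted 0.05 with neither named decisive, and Hypothesis 3 has a simultaneous and an individual route with no order between them

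*Protocol article*

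**What the plan says.** Specific aim 1 puts two targets side by side without ranking them: "Our first aim is to determine the effectiveness and efficacy of 3-month use of MS INFoRm on fatigue impact among persons with MS". The Statistical analysis section then states one Hypothesis 1 and one level: "A *p* < 0.05 will be used as the significance value". Two analyses follow.

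- Efficacy: "In order to test efficacy, or whether MS INFoRm works when delivered as intended, data from only those individuals" with complete baseline and 3-month data who also opened all of the site's content at least once.
- Effectiveness: "In order to test effectiveness, participants who have missing 3-month scores will be assigned a change score of zero".

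Hypothesis 2 is handled more tightly. It names only the zero-change version ("The analysis will use the same approach as hypothesis 1, using zero-value change scores for individuals lost to follow-up") and divides the level by the number of outcomes ("therefore the significance value will be set at *p* < 0.0125 (0.05/4 tests").

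For Hypothesis 3 each mixed model has "a random intercept and terms for both a linear and quadratic trend", and "The five measures (MFIS, MSSES, PDQ, CES-D, and IPA) will be modelled simultaneously and individually". The simultaneous model is read at 0.05 and the individual models at 0.01, given as 0.05/5. No order or dependence between the two is stated.

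The Dissemination plan makes wider release of the website depend on the hypotheses being supported.

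**The concern.** Hypothesis 1 is a single claim that can be reached by two tests on different sets of participants with different rules for missing scores. If they disagree, the article does not settle whether the hypothesis is supported. A trial with a null as-randomised comparison could still report a positive primary hypothesis from the efficacy set, and by the Dissemination plan that claim bears on whether the website is rolled out.

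The efficacy set is also formed after randomisation, by a rule that asks different things of the two arms. The intervention site has seven sections, goal tracking, worksheets and separate pages on five influencing factors. The usual care site has short descriptions and links to two brochures. If the rule is applied to both arms, those who meet it need not be comparable between arms, so the second route lacks the protection of randomisation.

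Hypothesis 3 has the same undefined decision rule in milder form: two routes, each with its own threshold, and no statement of which one counts.

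**Working it through.** **The plan's own figures.** 0.05/4 = 0.0125 and 0.05/5 = 0.01. Both are reproduced exactly. Five tests at 0.01 have a bound of 5 × 0.01 = 0.05 and, if independent, 1 − 0.99^5 = 0.0490. Each divisor is right within its own family.

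**Hypothesis 1, either test at 0.05 (two-sided assumed).**

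- Bound: 0.05 + 0.05 = 0.10. If independent: 1 − 0.95² = 0.0975.
- The tests are not independent, because the efficacy set lies inside the randomised set. If it is a random fraction f of the participants analysed, the two test statistics have correlation √f, and the either-test error is 1 − P(|Z1| < 1.96 and |Z2| < 1.96):

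| f | correlation | either test significant under no effect |
|---|---|---|
| 0.30 | 0.548 | 0.089 |
| 0.40 | 0.632 | 0.086 |
| 0.50 | 0.707 | 0.083 |
| 0.75 | 0.866 | 0.073 |
| 0.90 | 0.949 | 0.065 |
| 1.00 | 1.000 | 0.050 |

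- This was checked by simulation with the article's numbers: 100 per arm; attrition of 34% (the upper figure in the Sample size section) or 10% (assumed); zero change for missing scores; and a mean change of 0 or −0.5 SD in both arms (assumed). Here the share is of completers:

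| Completers who qualify | either test significant |
|---|---|
| 100% | 0.047–0.052 |
| 75% | 0.065–0.076 |
| 50% | 0.079–0.083 |
| 25% | 0.084–0.093 |

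Taken singly, the effectiveness test rejected in 0.038–0.052 of runs and the efficacy test in 0.047–0.053. The excess therefore comes from having two chances. Qualifying was made unrelated to outcome, so no selection bias is included.

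**Hypothesis 3, simultaneous at 0.05 or any individual at 0.01.**

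- Bound: 0.05 + 5 × 0.01 = 0.10. If independent: 1 − 0.95 × 0.99^5 = 0.0966.
- Simulation used five outcomes with correlation 0 to 0.7 between them, within-person correlation 0.5 or 0.7, visits at months 0, 3 and 9, and a 2-df group-by-trend test per outcome. The five individual tests together gave 0.036–0.049, the simultaneous test about 0.05, and either route 0.070–0.075.
- If the simultaneous test must be significant before the individual ones are read, any false claim under the global null requires that test to reject, so the error is at most 0.05.
- The excess arises only under the global null. If at least one outcome truly differs, a significant simultaneous test is not a false claim, and the individual tests of the remaining outcomes (at most four) have a bound of 4 × 0.01 = 0.04.

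**The case against.** The strongest reply on Hypothesis 1 is that effectiveness and efficacy are different questions with different data sets, a familiar pairing. Reported each under its own label, each test keeps its 0.05. The text also leans towards effectiveness: it ties intention to treat to that analysis, explains its real-world advantage, and carries only the zero-change rule into Hypothesis 2. Ranking analyses is often left to an analysis plan, which is not shown.

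Part of this stands. The inflation is conditional on letting either result support Hypothesis 1, and the article does not say that it may. But the article itself fixes the populations, thresholds and divisors, places both analyses under one hypothesis at one level, and links roll-out to the hypotheses being supported. A lean is not a rule for discordant results.

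On Hypothesis 3, a simultaneous model followed by individual ones can be read as an omnibus test with follow-ups, which would hold 0.05. The article states no such order. The excess is small, and it concerns a third aim that presupposes an earlier effect, so the global null may not be the most relevant case.

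A reader might also infer that each individual model is tested twice, once per trend term, making ten tests where the plan counts five. The article does not support this. It says that each model contains both terms, not that each is tested separately, and its own count is one test per measure. With one contrast or one 2-df test per outcome, 0.01 is the right level. The article does leave the deciding term unnamed, and that is worth fixing.

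**Conclusion.** The point holds as an undefined decision rule. It would be too strong to say that the stated error rates are not held: every divisor is correct within its family, and the article claims no combined rate across the two Hypothesis 1 analyses or the two Hypothesis 3 routes.

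For Hypothesis 1, if either analysis may support the claim, the type I error is about 0.065 to 0.09 (bound 0.10), falling to about 0.05 if nearly all participants qualify for the efficacy set. The share who qualify is an assumption, since the article gives none. Selection bias would come on top and is not quantified here. For Hypothesis 3, the error is about 0.07 if either route can claim success and at most 0.05 under the global null if the simultaneous test is a gate. That rests on assumed correlations and on one deciding test per outcome.

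The Hypothesis 1 part matters more, because it determines what the trial may conclude on its primary outcome. The change should be made before the data are analysed.

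**What to change.** For Hypothesis 1, state that the as-randomised effectiveness contrast in MFIS change at 3 months is the only confirmatory test. Report the efficacy analysis as supportive, with an estimate and confidence interval and no significance claim. If the investigators want both analyses to be able to claim success, a Bonferroni split would put each at 0.05/2 = 0.025, but that would not remove the selection problem in the efficacy set.

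For Hypothesis 3, name one deciding test per outcome (one contrast or one 2-df test) at 0.01. Then state either that the simultaneous model at 0.05 must be significant before the individual results are read, or that it is descriptive.

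This takes a few sentences and needs no new data or change in sample size. The downside is that a positive efficacy result on its own could no longer carry the primary claim.
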